## Methods

### Study design

The study will be a randomized controlled trial (RCT) investigating the efficacy of guided Internet-based treatment for patients with panic disorder in comparison to a CAU group. As shown in Fig. 1, the study design is a parallel-design randomized waitlist-controlled clinical trial. Participants in the intervention group will receive access to the intervention (i.e., Invirto) right after t0, while the CAU group will receive access to Invirto after the first intervention period of 3 months (t1). Participants will be assessed online via the online survey platform Qualtrics® at baseline (t0), post intervention (t1, 3 months after baseline), and follow-up (t2, 6 months after baseline). See Table 2 for a schedule of enrollment, interventions, and assessments.

**Fig. 1 Fig1:**
[figure not shown]
Study flow

**Table 2 Tab2:** Schedule of enrollment, intervention, and assessments

	**Study period**			
**Time point**	**t-1 Enrollment**	**t0 baseline assessment**	**t1 post assessment**	**t2 follow-up assessment**
***Eligibility screen***	X			
***Informed consent***		X		
***Randomization***		X		
**Access to intervention**				
Invirto (intervention group)		X		
Care as usual (control group)			X	
**Primary outcome measures**				
Beck Anxiety Inventory (BAI)		X	X	X
**Secondary outcome measures**				
Panic and Agoraphobia Scale (PAS)		X	X	X
Beck Depression Inventory-II (BDI-II)		X	X	X
Questionnaire on panic-related Anxieties, Cognitions and Avoidance (ACA)		X	X	X
The Acceptance and Action Questionnaire-II (AAQ-II)		X	X	X
Quality of Life–global item (WHOQOL-BREF)		X	X	X
Questionnaire to evaluate patient satisfaction (CSQ-8)			X	X
Treatment Adherence Perception Questionnaire (TAPQ-adapt)			X	X
Positive and Negative Effects of Psychotherapy Scale (PANEPS-I)			X	X
Peritraumatic Dissociative Experiences Questionnaire (PDEQ-adapt)			X	X

### Sample size

In a meta-analysis published by Haug, Nordgreen, Öst, and Havik [20] on the effectiveness of iCBT interventions for treatment of anxiety, a mean effect size compared to waiting control groups of Hedges’ *g* = 0.55 (≈ *f* = 0.28) was found. A power analysis with the software G*Power [29] resulted in a target sample size of *N* = 103 to detect a medium-sized effect (*f* = 0.28) with *α* = 0.05 and a power of 0.80 for an ANCOVA. Using an assumed drop-out rate of 20% based on meta-analytic data on comparable studies [20], we will aim to recruit *N* = 128 participants.

### Recruitment

Information about the study will be given on the study’s website. Flyers and social media posts will be created. Interested study participants will be able to contact Sympatient Ltd. via the study website, by telephone, or by sending an e-mail. After verifying the technical requirements for participation via telephone (e.g., smart phone access), those who remain interested in participating in the study will be required to obtain a consultation report from their primary care physician prior to consenting to study participation to confirm that no physical exclusion criterion that could stand in the way of participation in the study (e.g., cardiovascular disease) is met. If the requirements are met, potential study participants will be referred to a clinician for a personal clinical diagnostic interview. This interview will be conducted in person or digitally via video call; participation in the study by telephone only is impossible. Inclusion is based on a classification diagnostic (DSM-5-SCID, American Psychiatric Association, 2014) that verifies the inclusion and exclusion criteria. After the inclusion and exclusion criteria have been verified, participants will receive a link to participate in the study on the digital study platform Qualtrics ®.

### Eligibility criteria

To be included, participants must meet all inclusion criteria and not fulfill any of the exclusion criteria listed below.

Inclusion criteria are as follows:Age between 18 and 80Provision of electronic informed consentPossession of a smartphone with Internet accessPanic disorder as verified by DSM-5-SCID interview.Panic symptoms experienced for at least 12 months

Exclusion criteria are as follows:Acute suicidality as assessed by the DSM-5-SCID interviewDiagnosis of schizophrenia or a bipolar disorder as verified by the DSM-5-SCID interview

### Randomization

To ensure balance between treatment groups (intervention or CAU group), randomization will be performed using the randomizer in the Qualtrics® survey flow. The 128 planned study participants will be allocated to the two conditions with an automatic ratio adjustment via Qualtrics® according to a predetermined allocation ratio of 1:1. After the t1 assessment, participants will be automatically randomized and notified about their group allocation. Since the present study assesses outcome by self-report questionnaires, no blinded outcome assessors are needed. Data analysts will not be blinded to randomization. After random allocation to a study group, participants will stick with their group. Upon participant request, participants are allowed to leave at any time.

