##### Adapted Peritraumatic Dissociative Experiences Questionnaire (PDEQ-adapt)

The PDEQ by Marmar et al. [48] is a standardized self-report 10-item questionnaire that retrospectively assesses dissociation, depersonalization, and derealization experiences during a traumatic event. Participants are asked to rate statements regarding dissociation on a five-point scale ranging from “(1) not at all true” to “(5) extremely true” at t1 and t2. An overall PDEQ score is calculated by summing the scores, with higher scores indicating more severe symptoms. Internal consistency shows a Cronbach’s *α* of 0.89 [48]. In the present study, we used an adapted version of the PDEQ (PDEQ-adapt) by reformulating the items to ask about dissociation during VR exposure instead of a past traumatic event.

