### Statistical analyses

The present study is designed to investigate the Invirto for patients with panic disorder. Intention-to-treat (ITT) analyses and complete case (CC) analyses are planned for statistical analyses. For the ITT analyses, this means that participants with all data available at t0 will be included in the statistical analysis and that missing values for t1 and t2 will be imputed using the multiple imputation (MI) procedure [49]. All hypothesis tests will be performed at a significance level of *α* = 0.05.

For primary analysis regarding symptom severity, data will be analyzed using analysis of covariance (ANCOVAs), with between-group differences over time (Invirto vs. CAU). Baseline scores will serve as covariates and group allocation as the independent variable. The dependent variable is the decrease in anxiety from time t0 to time t1 operationalized by the BAI sum score (primary outcome). The procedure for conducting the ANCOVA is guided by Field, Miles, and Field (2012). Before testing the hypothesis, the prerequisites of the ANCOVA will be checked.

The analysis regarding the secondary parameters will follow the analysis rationale of the primary outcome.

Partial eta square (η_p_
^2^) and Cohen’s *d* will be calculated as effect sizes. Group differences at baseline will be assessed using chi-square tests and independent *t*-tests for continuous variables. All analyses will be conducted using IBM SPSS Statistics® 27.

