## Discussion

The present study aims to investigate the efficacy of the Internet-based intervention Invirto for panic disorder using a randomized controlled design. Evidence shows that Internet-based interventions can be effective in reducing anxiety symptoms [21]. Invirto aims at reaching those who do not seek conventional face-to-face therapy, thus narrowing the existing treatment gap. We expect that Invirto will be superior to CAU in reducing anxiety-related and depressive symptoms, overall quality of life, and avoidance behavior.

Still, the trial has some limitations that need to be acknowledged. First, the ratings regarding psychological symptomology (not diagnostic status) rely on self-ratings. While self-ratings come with several disadvantages (e.g., social desirability; [50]), they have the benefit of reducing drop-out rates due to fear of stigmatization, which may be particularly high in patients seeking help in digital interventions. Second, the study design’s inclusion of a CAU control group instead of an active control group comes with the disadvantage of not being able to eliminate the expectancy effect [51]. However, the common first step is to compare a treatment to a no-treatment waiting control group. Furthermore, the data analysts will not be blinded and there will be no external data management committee as this would require further funding for an independent data analysis. This might lead to the risk of bias in regard to data analysis.

Compared to traditional face-to-face therapy, Invirto has several benefits, including high flexibility of time and location and low-threshold access to digital psychotherapy without long waiting periods. In addition, Invirto has the major strength of being one of the first programs to include self-managed exposure therapy in VR. Therefore, the role of self-applied VR for exposure therapy in digital psychotherapy will be highlighted in the study. Furthermore, Invirto is based on CBT, which is the guideline-recommended psychotherapy for panic disorder [7].

Future practical implications and potential possibilities of Internet-based interventions for anxiety disorders will be discussed. Invirto may be able to help those who cannot access psychotherapy (due, for example, to geographical distance or long waiting times) or who avoid face-to-face-therapy due to stigma.

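### Analysts are left unblinded, yet masking the arm code in-house needs no independent analysis and would reduce, though not remove, the bias risk the authors concede

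*Protocol article*

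**What the plan says.** The Randomization section of the protocol article says "Data analysts will not be blinded to randomization" and gives no reason there. The same section has participants told their allocation, and it dispenses with blinded assessors because outcomes are self-reported.

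The Discussion returns to the matter as a limitation: "the data analysts will not be blinded and there will be no external data management committee as this would require further funding". The sentence goes on to say that the funding would be for an independent data analysis. The next sentence accepts the consequence: "This might lead to the risk of bias in regard to data analysis".

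The Statistical analyses section plans two analysis sets ("Intention-to-treat (ITT) analyses and complete case (CC) analyses are planned for statistical analyses") and a check of the data before the test ("Before testing the hypothesis, the prerequisites of the ANCOVA will be checked"). The primary model is simple: "Baseline scores will serve as covariates and group allocation as the independent variable".

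No masked arm code, and no lock of the analysis before unmasking, is described.

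**The concern.** The choice is stated outright, so it is not a detail merely left to another document. The reason offered does not lead to it. If cost is the obstacle to blinding, the obstacle is an outside analyst, and blinding does not need one. Someone at the study center can recode the arm and hold the key while the same in-house analyst does the work.

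It matters more here than in many trials. Participants know their arm, the outcomes are self-reported, and there is no external committee. The analysis stage is the main point at which masking is still possible. An analyst who can see which arm is Invirto while fitting the imputation model or reacting to an assumption check can be influenced by the direction of the result, even without intending it. That is the risk the Discussion admits.

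**Working it through.** **1. The two statements side by side.** Randomization fixes unblinded analysts. The Discussion names a funding reason tied to an independent analysis. Masking would need three things: an allocation variable, someone other than the analyst to recode it, and an analysis that runs on the recoded variable. Allocation is made electronically by the Qualtrics randomizer (Randomization), and the study center collects and manages the data (Data collection and management). The third is checked next.

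**2. Does the primary analysis need to know which arm is which?** Its inputs are BAI at t0, BAI at t1 and group. Write the model as

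change = b0 + b1 × baseline + b2 × group.

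Exchanging the labels A and B reverses the sign of b2 and leaves its size and standard error alone, so F = (b2/SE)² is unchanged. The ANCOVA prerequisites that involve group can be checked on A/B codes in the same way.

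**3. Does masking touch the planned size or power?** The plan's own figure is reproduced first. Inputs from Sample size: f = 0.28 (from g = 0.55; 0.55/2 = 0.275), alpha 0.05, power 0.80. One covariate and two groups are assumed.
- Noncentrality = N × f² = 103 × 0.0784 = 8.08, with 1 and 103 − 3 = 100 degrees of freedom.
- Power at N = 103 is 0.804; at N = 102 it is 0.7996. The stated 103 is confirmed.
- Dropout: 103 / 0.80 = 128.75, or 129 rounded up, against the stated 128 (128 × 0.80 = 102.4 evaluable). The difference is immaterial.

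None of these quantities depends on who knows the arm code, so masking leaves them unchanged.

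**4. How well would the mask hold?** With 103 evaluable participants split equally, the standard error of a standardised difference is about √(4/103) = 0.197. The planned effect is then 0.55 / 0.197 = 2.79 standard errors (√8.08 = 2.84 using f = 0.28). If that effect is real, the better-scoring arm is Invirto with probability Φ(2.79) ≈ 0.997. Once group means are on the screen, A/B coding hides little. The code protects mainly the decisions taken before that moment, so the syntax has to be fixed first.

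**5. Which variables would reveal the arm at once?** Table 2 schedules CSQ-8, TAPQ-adapt, PANEPS-I and PDEQ-adapt at t1, when the CAU arm has not yet had the app. PDEQ-adapt, for one, was made by "reformulating the items to ask about dissociation during VR exposure instead of a past traumatic event". App-use data would do the same. BAI, PAS, BDI-II, ACA, AAQ-II and the WHOQOL item are taken at baseline in both arms and do not carry this problem.

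**6. Is there still time?** Trial status says that 115 participants had completed baseline, that no data had been extracted or analysed at submission, and that later changes would be recorded as an amendment.

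**The case against.** The strongest reply is that nothing here is wrong on its face. The choice is stated, repeated as a limitation, and its risk conceded. No figure is miscalculated and no passage contradicts another. That stands, and it sets the grade of the point.

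Several stronger readings are tempting and are not supported.

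- *A reader might infer that masking would remove the bias.* Step 4 shows otherwise. Unequal dropout could also reveal the arm, and much of the protection comes from fixing the syntax beforehand, which helps with or without a mask.
- *A reader might infer that the authors give funding as their ground for not blinding the analysts.* The clause follows two statements joined by a conjunction and may refer mainly to the external committee. On that reading the unblinded analysts have no stated reason at all, and the suggestion is unaffected. The article nowhere calls the risk unavoidable.
- *A reader might count the imputation model, the response to failed ANCOVA checks and the ranking of the two analysis sets as steps shown to be open.* The article does not settle them, but an analysis plan not shown here may do so. They illustrate where knowledge of the arm could act; they are not shown to be gaps.
- *A reader might take the cost as established to be negligible.* The documents give no cost figure and do not say who could hold the key or whether the analysts have already seen allocations. That the change is cheap is a judgement from the nature of the task.

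**Conclusion.** The point holds in a limited form. The protocol declines analyst masking and concedes the resulting risk, and whatever funding an independent analysis would need does not rule out an in-house masked analysis. Masking would reduce that risk at no loss of power, alpha or sample size. It would not eliminate it, and it does nothing about self-report bias from participants who know their arm.

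The size of the bias cannot be derived from the documents, and no claim is made that the result will be biased. The conclusion assumes that someone at the study center other than the analyst can recode the file, and that the analysts have not yet worked with outcomes by arm. The second is consistent with the trial status at submission but is not guaranteed afterwards. The point is a cheap improvement to a disclosed choice.

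**What to change.** Replace the sentence on analyst blinding under Randomization with text to this effect:

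*The imputation model and analysis syntax will be fixed and dated before any group-wise outcome is viewed. The primary BAI analysis and the analyses of the secondary outcomes measured at baseline (PAS, BDI-II, ACA, AAQ-II, WHOQOL global item) will be run on a file in which study-center staff other than the analyst have coded the arms A and B and hold the key. CSQ-8, TAPQ-adapt, PANEPS-I, PDEQ-adapt and app-use data will be withheld from the analyst until the code is broken.*

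Amend the limitation in the Discussion to match: analysts masked to the arm code up to the lock of these analyses, masking partial, no external committee. If analysts have already seen outcomes by arm when the amendment is made, it should say so.

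The cost is one recoding step, a named holder of the key, and an analysis in two stages, with the withheld instruments analysed second. No participant, visit or recruitment step is affected.

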### Intervention

If a study participant is assigned to the intervention group, they will receive access to treatment with the Invirto right after baseline assessment (t1). Invirto provides iCBT for anxiety in eight modules with low-threshold therapeutic support. The contents of Invirto are in line with national treatment guidelines for anxiety disorders [6], which are based on established German and international CBT treatment manuals for anxiety disorders [30–33]. All content of Invirto is presented via an e-health tool (i.e., an app), including audio and video lessons recorded with experienced psychotherapists, behavioral exercises in virtual reality, and exercises for cognitive restructuring and transfer of content to everyday life. For their autonomous implementation of the app (e.g., at home), patients receive virtual reality glasses, headphones, instructions for use, and an access code for the Invirto app. The app contains approx. 15 h of content. In addition, all patients receive two video-conference individual sessions with clinical psychologists (each approx. 50 min). In the first personal contact, the therapist practices an initial guided exposure exercise with the patient and prepares them to continue self-directed exposures. Aside from the interactions within the app, there are no further prompting strategies or push notifications. Invirto uses regular check-ins; if the user appears suicidal, offers of help are provided. After all the content in the Invirto app has been completed, the treatment is reviewed, strategies for relapse prevention are discussed, and the user prepares with the therapist for the time after the treatment concludes in the second videoconference. Invirto ends with this final session, but patients still have access to the content of the Invirto app for one more year and are digitally prompted by the software to continue practicing.

### Measures

#### Primary outcome measures

##### Beck Anxiety Inventory (BAI)

The primary outcome is the improvement in anxiety symptoms as measured by the German version of the Beck Anxiety Inventory [34] from t0 to t1. The BAI is a self-report measure of anxiety severity that has 21 items on anxiety-associated sensations and cognitions, which are assessed in terms of their intensity over the previous week on a four-point Likert scale. The BAI scores are classified as minimal anxiety (0 to 7), mild anxiety (8 to 15), moderate anxiety (16 to 25), and severe anxiety (30 to 63). The BAI is regarded as reliable (*α* = 0.90) and valid as well as change sensitive [34, 35].

#### Secondary outcome measures

##### Panic and Agoraphobia Scale (PAS)

The Panic and Agoraphobia Scale (PAS; [36]) measures the symptom severity of panic disorder (with or without agoraphobia) within the past week. Thirteen items with a five-point Likert scale are used to assess five domains that limit quality of life in patients with panic disorder: panic attacks, agoraphobic avoidance, anticipatory anxiety, restriction, and health fears. Scores range from 0 to 52, with higher scores indicating higher levels of panic (0–8 = no panic, 9–18 = minimal panic, 19–28 = moderate panic, 29–39 = severe panic, and scores ≥ 40 = very severe panic). The PAS is considered a reliable (Cronbach’s *α* = 0.86) and valid test instrument [36]. In the present study, it will be assessed at t0, t1, and t2.

##### Beck Depression Inventory-II (BDI-II)

The Beck Depression Inventory-II (BDI-II; [37]) is a 21-item self-report questionnaire that assesses depressive symptoms over the previous 2 weeks. In the present study, it will be assessed at t0, t1, and t2. Scores range from 0 to 63, with higher scores indicating higher levels of depression (0–8 = no depression, 9–13 = minimal depression, 14–19 = mild depression, 20–28 = moderate depression, and 29–63 = severe depression). Internal consistency is good, with Cronbach’s *α* = 0.89 [38].

##### Questionnaire on panic-related Anxieties, Cognitions and Avoidance (ACA)

The Questionnaire on panic-related Anxieties, Cognitions and Avoidance (ACA [39]) is a self-report questionnaire consisting of three different subdomains: Body Sensations Questionnaire (BSQ; rating of the severity of 17 physical symptoms, such as palpitations), Agoraphobic Cognitions Questionnaire (ACQ; assessment of the frequency of 14 catastrophizing thoughts that occur when the person is anxious), and Mobility Inventory (MI; extent of avoidance of 27 situations that are often anxiety-provoking for patients with agoraphobia). The questionnaire shows good to very good consistencies and retest reliabilities (Cronbach’s *α* = 0.79–0.96). The instrument set has also been proved sensitive to the measurement of therapy effects [39]. In the present study, it will be assessed at t0, t1, and t2.

##### The Acceptance and Action Questionnaire-II (AAQ-II)

The Acceptance and Action Questionnaire-II (AAQ-II; [40]) is a questionnaire that aims to measure experiential avoidance and psychological flexibility, such as negative evaluations of feelings (e.g., “Anxiety is bad”) and avoidance of thoughts and feelings (e.g., “I try to suppress thoughts and feelings that I don’t like by just not thinking about them”). The questionnaire consists of seven items with a seven-point Likert scale from “(1) never true” to “(7) always true”. Internal consistency shows a Cronbach’s *α* of 0.84 for social phobia patients and 0.97 for students in the German version [41]. In the present study, it will be assessed at t0, t1, and t2.

##### Quality of Life—global item (WHOQOL-BREF)

The Quality of Life–global item (WHOQOL-BREF; [42]) is a cross-cultural questionnaire assessing generic quality of life. It was developed by the WHOQOL Group of the World Health Organization. The internal consistency of the questionnaire is acceptable (*α* = 0.7 [43]). For the present study, we will use the global QoL item, with answers ranging from “(1) very poor” to “(5) very good”, at t0, t1, and t2.

